**Study protocol (version 1)**

**Validation of a novel non-invasive technique based on real time ultrasound B-mode to assess the jugular venous pulse**

**OVERALL SUMMARY**

The jugular venous pulse (JVP) reflects changes in the right atrial pressure and its evaluation can be useful in managing many emergency conditions as well as in the diagnosis and/or prognosis of many heart and lung diseases. It is traditionally evaluated by a physical examination that visually analyzes the change in volume of the internal jugular vein (IJV) whilst also providing an estimate of the central venous pressure (CVP), though with a low accuracy. Furthermore, the real CVP is measured invasively through the cannulation of the venous system, thus not feasible as a routine approach. We hypothesized that it is possible to derive the JVP waveform through the ultrasound B-mode sequential assessment of the cross-sectional area of the IJV along the cardiac cycle. A preliminary pre-clinic study was performed to develop a proper method and to assess its accuracy and internal validity. The present project aims to fully implement and validate this new method and to test its transferability into a clinical setting.

**BACKGROUND AND STATE OF THE ART**

The evaluation of the jugular venous pulse (JVP), defined as the movement of expansion of the jugular veins due to changes in pressure in the right atrium, provides valuable information about cardiac hemodynamics and filling pressures (1), characteristic wave patterns pathognomic of cardiac diseases (2), and an indirect estimate of the central venous pressure (CVP). The JVP evaluation can be useful in managing many emergency conditions for guiding the fluid administration as well as in the diagnosis and/or prognosis of many heart (3) and lung diseases, notwithstanding it is often neglected by clinicians (2). JVP is traditionally evaluated by a physical examination that visually analyzes the change in volume of the internal jugular vein, with variable inclination of the upper body and the sternal angle as the reference point (4). However, it is considered a misunderstood and difficult physical technique (5) and the accuracy of the estimated CVP is no better than 50–60% (6). Besides, the real CVP is measured invasively through the cannulation of the venous system, thus not feasible as a routine approach. Several methods have been reported aiming to measure JVP and CVP either non-invasively or in a minimally invasive approach (6-9) but none showed enough accuracy and precision (6), neither completeness of information provided for clinicians, nor ease of use to enter into the routine clinical practice.

We therefore hypothesized that it is possible to derive the JVP waveform through the ultrasound B-mode sequential assessment of the cross-sectional area of the IJV along the cardiac cycle. A preliminary pre-clinic study had already been performed in collaboration with the Department of Physics of the University of Ferrara to develop the technical feasibility of this evaluation and to assess its accuracy and internal validity (10). Such methodology would also allow, through an algorithm and software, the ability to derive and analyze the waveform in post-processing, whilst already at the bedside, minimizing the evaluation time required and reducing the possible technical difficulties for the operator. The present project aims to fully implement and validate this new method and to test its transferability into a clinical setting.

**AIM OF THE STUDY**

**AIM 1**: To validate in a clinical setting a novel non-invasive technique based on real time ultrasound B-mode to assess the JVP (bed-side post processing analysis).

**AIM 2**: To verify if the proposed method can be transferred from our hemodynamics and fluid dynamics lab to the clinical setting, by using any kind of US equipment widely available in any hospital in our Country, and implemented by operators without a specific qualification in US technique, but after appropriate training.

**EXPERIMENTAL DESIGN AIM 1**

Aim 1 will be divided into 2 phases.

Phase 1: improvement and refinement of US-JVP software usability.

In a preliminary experiment (10) the variation of the cross-sectional area of the IJV during the cardiac cycle by means of real time B-mode images sequence was studied, and a resultant waveform trough time was outlined. It was also verified if an automatic procedure could reliably substitute a time inefficient operator tracing. Thanks to an algorithm and the development of a related original software, it was tested that the assessment of this waveform can be performed in post-processing analysis. This first phase of the project will be devoted:

a) To improve the usability of the algorithm and related software.

b) To study the relationship between variations of IJV cross sectional area and variations of IJV inside pressure in order to develop a physical model providing an estimate of the CVP.

c) To study the different waveforms derived from the US-JVP outlining a pool of normal or potential diagnostic abnormal patterns.

This will lead to further refinement of the algorithm and the related software in view of the Phase 2 of the project and the final validation of the US-JVP technique. This first phase will be carried out by close collaboration among physicists and clinicians.

Setting

OU of Translational Surgery and OU of University Anesthesiology and Intensive care, University Hospital of Ferrara and Eco-Fluid dynamics lab of the Department of Physics, University of Ferrara.

Subjects

At least n=80 consecutive healthy adult subjects of different sex and age will be studied by means of US-JVP technique. This number of subjects will likely allow us to detect and to evaluate the different morphological subtypes of IJVs.

Inclusion criteria: adult subjects (> 18 years).

Exclusion criteria: current acute disease, chronic cardiac or lung diseases, neurodegenerative diseases, pregnancy.

At least n=50 consecutive spontaneously breathing hospitalized patients requiring a scheduled, or with deferred emergency, measurement of CVP by direct cannulation, will be also studied at bedside by means of US-JVP. In particular, a portion of this sample (n=25) will include patients affected by various cardiac pathologies (e.g. congestive heart failure, atrial septal defect, tricuspid regurgitation, atrial fibrillation, tricuspid stenosis, AV blocks, constrictive pericarditis) in order to outline different US-JVP waveforms patterns with a potential diagnostic power.

Inclusion criteria: hospitalized adult > 18 years in spontaneous breathing requiring a direct measurement of the CVP, scheduled or in a deferred emergency. Part of this sample will include patients affected by cardiac diseases (e.g. congestive heart failure, atrial septal defect, tricuspid regurgitation, atrial fibrillation, tricuspid stenosis, AV blocks, constrictive pericarditis)

Exclusion criteria: no clinical exclusion criteria. Pregnancy.

The sample size has been determined considering the potential recruitable healthy subjects and patients referred to the intensive care unit, the workload actually sustainable by the investigators and the need for the scientific aim of the research (e.g. n=50 measurements will allow obtaining a JVP waveform derived from about 6000 tracing by hand in order to refine the algorithm that is the basis of the US-JVP software automatic procedure).

Methods

US-JVP acquisition imaging: all subjects, in supine position with the neck latch on the longitudinal axis and tilted 45° backward, will undergo US scanning (B-mode images sequence) of the right and left IJVs using a probe linear array 7.5-11 MHz. After the correct image acquisition, for each neck side a clip of 30” will be recorded. US assessments will be performed by a skilled operator blinded to clinical conditions of the hospitalized patients and to subsequent measures of invasive CVP.

Estimated total time for US assessment is 5’. Immediately afterwards, in hospitalized patients, CVP assessment by direct cannulation of the venous system will be performed by competent staff operators according to the standard.

Phase 2: Full validation process of the improved US-JVP measurements

The validation processes will include assessment of the diagnostic power of the US-JVP estimated CVP values and US-JVP waveforms, including evaluation of sensibility, specificity, predictive positive and negative values, accuracy and precision, compared to the gold standard of direct invasive measurement of CVP.

Setting

OU of Translational Surgery and OU of University Anesthesiology and Intensive care, University Hospital of Ferrara and Eco-Fluid dynamics lab of the Department of Physics, University of Ferrara.

Subjects

n= 150 consecutive hospitalized spontaneously breathing patients requiring a scheduled, or with deferred emergency, measurement of CVP by direct cannulation.

Inclusion criteria: hospitalized adult > 18 years in spontaneous breathing requiring a direct measurement of the CVP, scheduled or in a deferred emergency.

Exclusion criteria: no clinical exclusion criteria. Pregnancy,

Methods

All patients will undergo a US scanning of the neck at bedside as described above, performed independently and sequentially by two skilled operators to verify the inter-observer reliability. To verify the test-retest reliability, operators will repeat the procedure twice and two 30”clips will be recorded. Operators will be blinded to the respective evaluations, to the clinical condition of the patient and to the subsequent measures of invasive CVP. Immediately afterwards CVP assessment by direct cannulation of the venous system will be performed by competent staff operators according to the standard.

For all the phases of the study, the measurement of CVP will not be carried out for experimental purposes but will be part of the scheduled plan for each subject during the hospitalization. Only the numerical data obtained will be considered for the purpose of this study. Therefore, no variation is expected with respect to the normal diagnostic-therapeutic pathway already defined for each study subject.

**EXPERIMENTAL DESIGN AIM 2**

Aim 2 will be developed in 2 phases.

The transferability of the new technique will be tested in an emergency clinical setting and in a specialized one. Four clinicians without specific expertise in the use of ultrasound technique will be involved in this project. They will be asked to use the new US-JVP technique, before (Phase 3) and after specific training (Phase 4).

Setting

OU of Translational Surgery, OU Emergency Service and OU Neurosurgery University Hospital of Ferrara.

Subjects: n = 40 consecutive patients requiring an evaluation of the JVP /CVP in scheduled or referred emergency.

Inclusion criteria: patients requiring an evaluation of the JVP/CVP in deferred emergency.

Exclusion criteria: no clinical exclusion criteria. Pregnancy,

Methods

This second part of the study will involve n=4 clinicians belonging to emergency and specialized operative units, without a specific skill in US evaluations. Clinicians will receive a basic explanation about the US-JVP technique and its modality of imaging acquisition.

Phase 3: Each clinician will evaluate n=10 subjects using US-JVP technique (independently, in different times and each one in their own context). Measurements recorded (twice for each neck side for assessing repeatability and reproducibility) will be compared to those ones immediately collected afterwards by a skilled operator.

Phase 4: The whole experiment will be repeated by the same clinicians, after a specific detailed training on US-JVP technique, to evaluate any difference in accuracy and precision with respect to phase 3.

The ultrasound evaluation will be additional to the normal diagnostic-therapeutic pathway defined for the patient who will therefore not undergo any substantial variation.

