**STATISTICAL ANALYSIS**

Aim1-Phase 1. Descriptive data will be expressed as the mean ± standard deviation or median and range according to the nature of the variables.

Aim1-Phase 2. The new US-JVP method will be compared to the gold standard of invasive CVP measurement in patients from an intensive care unit, with operators blinded to the patient’s condition and values of the direct measure of CVP. The number of patients required to estimate sensitivity and specificity, in a target population with a prevalence of 50%, assuming a clinically acceptable width of the 95% confidence interval of 10%, and a sensitivity and a specificity at least both of sizes 0.80, is 123. In order to correct for missing values, we will collect 20% patients more for a total sample size of 150 (11). Correlation between the two methods (US-CVP) will be analyzed using Pearson’s coefficient. The Bland-Altman method will be used to analyze the agreement between the measurements. The validation processes will assess the diagnostic power of the US-JVP evaluating sensitivity, specificity, predictive positive and negative values, accuracy and precision. Receiver operating characteristic (ROC) curves will be used to assess the sensitivity and specificity corresponding to different cutoffs for the new US-JVP method. Inter observers and test-retest reliability will be also calculated.

Aim 2 – Phase 3. The sample size needed to assess reliability between operators is based on Walter et al. (12). Assuming a minimally acceptable level of reliability of 0.60, given an alternative hypothesis of a level of reliability of 0.80, an alpha level of 0.05, a power of 0.80, a total of 40 patients are necessary to be evaluated independently by each clinician. Intraclass correlation coefficient (ICC) will be determined.

Aim 2 – Phase 4. Intraclass correlation coefficient (ICC) will be determined after the training. The Bland-Altman method will be also used to analyze the agreement between clinicians.

The statistical approach and analysis will be followed and carried out by statisticians of the Department of Public Health, Experimental and Forensic Medicine, Unit of Biostatistics and Clinical Epidemiology, University of Pavia

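### Aim 2 promises a change in accuracy, but its only comparator is a skilled operator's scan, so it can show agreement with that operator and not accuracy for CVP

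*Protocol*

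**What the plan says.** - **Aim 1 reference.** In EXPERIMENTAL DESIGN AIM 1, Phase 2, the validation covers diagnostic performance, including "accuracy and precision, compared to the gold standard of direct invasive measurement of CVP". STATISTICAL ANALYSIS repeats this: "The new US-JVP method will be compared to the gold standard of invasive CVP measurement in patients from an intensive care unit".
- **Aim 2 comparator.** In EXPERIMENTAL DESIGN AIM 2, Phase 3, the measurements of four clinicians without ultrasound expertise "will be compared to those ones immediately collected afterwards by a skilled operator".
- **Aim 2 target.** Phase 4 has the same clinicians repeat the experiment after training, "to evaluate any difference in accuracy and precision with respect to phase 3".
- **Aim 2 analysis.** In STATISTICAL ANALYSIS, for Phase 3: "Intraclass correlation coefficient (ICC) will be determined". Phase 4 has the ICC again, and "The Bland-Altman method will be also used to analyze the agreement between clinicians". Neither phase has an analysis that involves invasive CVP.
- **Routine CVP.** The Aim 1 Phase 2 methods contain a general sentence: "For all the phases of the study, the measurement of CVP will not be carried out for experimental purposes". The text goes on to say that CVP belongs to the patient's planned care and that only its numerical value is used.
- **Aim 2 eligibility and setting.** Patients must need an evaluation of JVP/CVP. Direct cannulation, an entry condition for the Aim 1 patients, is not required. The units listed are Translational Surgery, Emergency and Neurosurgery.

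**The concern.** The same pair of words has invasive CVP as its reference in Aim 1 and another user's scan with the same technique in Aim 2. The protocol does not flag the change. Agreement between two users of one index test is reproducibility. A good ICC, or an ICC that rises after training, says that clinicians have come closer to the skilled operator. It does not say how close either of them is to CVP.

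At stake is what Aim 2 may conclude. TRANSLATIONAL RELEVANCE AND IMPACT FOR THE NATIONAL HEALTH SYSTEM foresees that, if results are positive, trained operators from several disciplines could use the technique to evaluate JVP and CVP. If the Phase 3 to Phase 4 result is reported under the name accuracy, readers will take it in the Aim 1 sense, which Aim 2 does not measure. A statistical analysis plan could define the term, but it could not analyse a CVP value that the Aim 2 design does not say to collect.

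**Working it through.** **1. What the Aim 2 sample size covers.** Inputs from STATISTICAL ANALYSIS: reliability 0.60 against 0.80, alpha 0.05, power 0.80, 40 patients. The Walter-Eliasziw-Donner formula is k = 1 + 2(z_alpha + z_beta)² n / [(ln C)² (n − 1)], with C = (1 + n·t0)/(1 + n·t1) and t = rho/(1 − rho).

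With n = 2 ratings, t0 = 1.5 and t1 = 4, so C = 4/9 and (ln C)² = 0.658. With a one-sided alpha (the protocol does not state sidedness), k = 1 + 2 × (1.645 + 0.842)² × 2 / 0.658 = 38.6, or 39. That is close to the stated 40. The figure is a two-rater reliability calculation with no CVP term.

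**2. Why shared error is invisible.** For one patient, write clinician = CVP + s + e1 and expert = CVP + s + e2, where s is an error common to both scans. The difference is e1 − e2, so s drops out of Bland-Altman. In the ICC, any part of s that varies between patients counts as between-patient variance and raises the coefficient.

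**3. What a clinician-expert correlation of 0.80 implies for CVP.** Assumptions: the ICC is treated as a correlation, and the expert's sensitivity and specificity are the 0.80 of the Aim 1 sample size, at 50% prevalence, under bivariate normality. For a median split, sensitivity = 1 − arccos(r)/π, so r(expert, CVP) = cos(0.2π) = 0.809.

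The three pairwise correlations must be mutually compatible, so r(clinician, CVP) lies within a·c ± √[(1 − a²)(1 − c²)], with a = 0.80 and c = 0.809:
- a·c = 0.647
- √[(1 − 0.640)(1 − 0.654)] = 0.353
- range 0.29 to 1.00

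Two error models inside that range:
- Conditional independence (all disagreement is clinician error, unrelated to CVP given the expert's reading): r = 0.647.
- Exchangeable raters (equal, independent errors around a common signal): r = 0.809, the same as the expert, by symmetry.

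| Assumed r(expert, CVP) | Possible r(clinician, CVP) | Conditional independence | Exchangeable raters |
|---|---|---|---|
| 0.81 | 0.29 to 1.00 | 0.65 | 0.81 |
| 0.60 | 0.00 to 0.96 | 0.48 | 0.60 |

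**4. What a CVP comparison in Aim 2 could deliver.** The number of patients with a usable CVP is unknown. Assume 40, 20 or 10 in a phase, with 50% prevalence and sensitivity 0.80. The 95% half-width for sensitivity is 1.96 × √[0.16/(N/2)]. The half-width for bias, in SD of the differences, is 1.96/√N.

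| Patients with CVP | Sensitivity half-width | Bias half-width (SD) |
|---|---|---|
| 40 | 0.18 | 0.31 |
| 20 | 0.25 | 0.44 |
| 10 | 0.35 | 0.62 |

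Even with all 40, this is descriptive only.

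**The case against.** The strongest reply is that the comparator is the right one. Aim 2 asks whether the method can be transferred to operators without an ultrasound qualification. The protocol works in two steps: skilled operators are validated against CVP, then novices are compared with a skilled operator. The comparator is named just before the Phase 4 sentence. This stands, and the reliability design should stay. It does not rescue the word accuracy. Chaining through Aim 1 needs an error model (step 3), and the patients differ: Aim 1 Phase 2 takes spontaneously breathing patients needing cannulation, and Aim 2 states neither condition.

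A reader might infer three stronger things that the documents do not support:

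- **That Aim 2 holds CVP values and ignores them.** The sentence "For all the phases of the study, the measurement of CVP will not be carried out for experimental purposes" sits in the Aim 1 methods. It cannot mean that every subject has a CVP, since Phase 1 includes at least 80 healthy subjects. It is better read as saying that no CVP is taken for research. Aim 2 eligibility drops cannulation, its setting omits the intensive care unit where the invasive measurements are made, and no CVP is scheduled near the scan.
- **That clinicians would lose accuracy by a known amount.** The 0.65 follows from one error model, and exchangeable raters give no loss. Nor is 0.60 a success scenario, because it is the null value of the reliability calculation.
- **That the proposal for clinical use rests on Aim 2 alone.** That section refers to positive results of the project as a whole.

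**Conclusion.** The point holds in a limited form. As written, Aim 2 cannot deliver a difference in accuracy in the Aim 1 sense. It delivers agreement with a skilled operator, which is useful for transferability but blind to error common to both scans. This follows from the text alone and needs no model.

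The consequence for CVP accuracy is indeterminate. At the design value of 0.80, and with an assumed expert-CVP correlation of 0.81, the clinician-CVP correlation is bounded only by about 0.29 and 1.00. The ends of that range need unusual error structures, so it shows what the design leaves open and is not a forecast. Aim 1 and the choice of comparator are unaffected. This is an inexpensive improvement that changes what Aim 2 may claim.

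**What to change.** In EXPERIMENTAL DESIGN AIM 2 and the Aim 2 paragraphs of STATISTICAL ANALYSIS:

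1. Name the Phase 3 and Phase 4 outcome agreement with the skilled operator, in place of accuracy.
2. Analyse it as clinician minus skilled operator, with bias and limits of agreement by phase alongside the ICC. The present Bland-Altman text speaks only of agreement between clinicians.
3. Limit the Aim 2 conclusion to that agreement and its change after training.
4. Where a patient's routine pathway happens to include an invasive CVP close in time to the scan, record it. Report clinician-minus-CVP and expert-minus-CVP bias and limits of agreement by phase, as secondary and descriptive, with the number of patients. If there are none, make no statement about the clinicians' accuracy for CVP.

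The cost is protocol wording, one recorded value where it already exists, and a small table. It adds no procedure and no patients. The downsides are a narrower Aim 2 claim and a CVP subset that may be small or empty.

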**STATISTICAL ANALYSIS**

Aim1-Phase 1. Descriptive data will be expressed as the mean ± standard deviation or median and range according to the nature of the variables.

Aim1-Phase 2. The new US-JVP method will be compared to the gold standard of invasive CVP measurement in patients from an intensive care unit, with operators blinded to the patient’s condition and values of the direct measure of CVP. The number of patients required to estimate sensitivity and specificity, in a target population with a prevalence of 50%, assuming a clinically acceptable width of the 95% confidence interval of 10%, and a sensitivity and a specificity at least both of sizes 0.80, is 123. In order to correct for missing values, we will collect 20% patients more for a total sample size of 150 (11). Correlation between the two methods (US-CVP) will be analyzed using Pearson’s coefficient. The Bland-Altman method will be used to analyze the agreement between the measurements. The validation processes will assess the diagnostic power of the US-JVP evaluating sensitivity, specificity, predictive positive and negative values, accuracy and precision. Receiver operating characteristic (ROC) curves will be used to assess the sensitivity and specificity corresponding to different cutoffs for the new US-JVP method. Inter observers and test-retest reliability will be also calculated.

Aim 2 – Phase 3. The sample size needed to assess reliability between operators is based on Walter et al. (12). Assuming a minimally acceptable level of reliability of 0.60, given an alternative hypothesis of a level of reliability of 0.80, an alpha level of 0.05, a power of 0.80, a total of 40 patients are necessary to be evaluated independently by each clinician. Intraclass correlation coefficient (ICC) will be determined.

Aim 2 – Phase 4. Intraclass correlation coefficient (ICC) will be determined after the training. The Bland-Altman method will be also used to analyze the agreement between clinicians.

The statistical approach and analysis will be followed and carried out by statisticians of the Department of Public Health, Experimental and Forensic Medicine, Unit of Biostatistics and Clinical Epidemiology, University of Pavia

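### The 95% confidence interval width of 10% stated for Phase 2 does not match 123 patients: 10 points is the half-width, and the interval at 0.80 is 20 points wide

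*Protocol*

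**What the plan says.** The Aim 1, Phase 2 paragraph of the STATISTICAL ANALYSIS section sizes the validation against invasive central venous pressure by the precision of sensitivity and specificity. It works "in a target population with a prevalence of 50"% and gives the precision target and the result together: a "clinically acceptable width of the 95% confidence interval of 10%, and a sensitivity and a specificity at least both of sizes 0.80, is 123". The 123 is then raised by 20% for missing values, to 150. The Phase 2 part of EXPERIMENTAL DESIGN AIM 1 carries that total forward as "n= 150 consecutive hospitalized spontaneously breathing patients requiring a scheduled, or with deferred emergency, measurement of CVP by direct cannulation".

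The protocol nowhere describes the 10% as a half-width, a margin of error or a plus-or-minus figure.

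**The concern.** The width of a confidence interval is the upper limit minus the lower limit. A reader who takes the sentence at its word expects an interval of about 0.75 to 0.85 around an estimate of 0.80. With 123 patients, half with the condition and half without, each of the two proportions rests on about 61 patients. That is too few for an interval so narrow.

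The sentence is the only justification given for the Phase 2 sample size, and it is the only precision target for sensitivity and specificity. It also presents the target as the precision that is clinically acceptable. If the label is wrong, those who approve the study or read its results are told that estimates will be twice as precise as they will be. If the label is right, the sample size does not deliver the stated requirement.

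**Working it through.** **Inputs**, all from the Aim 1, Phase 2 paragraph of STATISTICAL ANALYSIS: confidence level 95% (z = 1.96); expected sensitivity and specificity p = 0.80; prevalence 0.50; precision figure 0.10; stated result 123; enrolment 150.

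**Formula.** The prevalence-adjusted normal-approximation formula is

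N = z² × p(1 − p) / d² / prevalence,

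where d is the half-width. At a prevalence of 50% the numbers with and without the condition are equal, so the same N serves sensitivity and specificity.

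**Step 1: reproduce the stated figure.** With d = 0.10:

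- patients with the condition: 1.96² × 0.8 × 0.2 / 0.10² = 61.5
- total: 122.9, rounded up to **123**

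This matches the protocol.

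**Step 2: take the wording literally.** A total width of 0.10 means d = 0.05:

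- patients with the condition: 1.96² × 0.8 × 0.2 / 0.05² = 245.9
- total: 245.9 / 0.5 = 491.7, rounded up to **492**

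This is four times the stated number.

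**Step 3: look for another route to 123.** A one-sided z gives 87 with d = 0.10 and 347 with d = 0.05. Treating all 123 patients as having the condition gives a total width of 14.1 points. None of these pairs a width of 10 points with 123.

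**Step 4: precision the design gives at 0.80.**

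| Evaluable patients | With the condition | Half-width (points) | Total width (points) |
|---|---|---|---|
| 123 | 61.5 | 10.0 | 20.0 |
| 150 | 75 | 9.1 | 18.1 |
| 492 | 246 | 5.0 | 10.0 |

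The result at 123 does not depend much on the interval method: the total width is 19.7 points by Wilson and 21.3 points by Clopper-Pearson.

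**Step 5: higher true accuracy at N = 123.** Total width = 2 × 1.96 × √(p(1 − p) / 61.5):

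| p | Total width (points) |
|---|---|
| 0.80 | 20.0 |
| 0.90 | 15.0 |
| 0.95 | 10.9 |

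A width of 10 points requires p(1 − p) = 61.5 × (0.05 / 1.96)² = 0.040, which gives p of about 0.96.

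**The case against.** The strongest defence is that this is loose vocabulary and nothing more. Every input is printed, a statistician can recover ±10 points from the sentence itself, and if that was the intention then sample size, enrolment and analyses are all unchanged. This stands as a limit on the consequences. It does not make the sentence correct, because the meaning can be found only by working back from the answer.

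A second defence is that 0.80 is a minimum and that 150 patients will be enrolled, so the interval may turn out narrower. This is true in part. However, the additional patients are there to replace missing values, and with none missing the width at 0.80 is still 18.1 points. Higher accuracy helps, but the stated width is reached only near 0.96, well away from the planning value.

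Two stronger readings are tempting, and the documents support neither:

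- **That an observed 0.80 could not support a claim of at least 0.80, or even of at least 0.70.** No interval of positive width around an observed 0.80 has its lower limit at 0.80, so 492 patients would not change this. The plan is to estimate, and 0.80 is a planning assumption; the paragraph sets no success threshold at 0.80 or 0.70. Whether the lower limit falls just below 0.70 also depends on the interval method: with all 150 evaluable it is about 0.71 by the normal approximation (0.80 − 0.09) and 0.69 by the exact method. The protocol does not name a method.
- **That the study has a quarter of the patients it needs.** This follows only if a total width of 10 points was truly the clinical requirement. The exact reproduction of 123 with a half-width of 0.10 points the other way, although the protocol alone cannot settle what was meant.

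**Conclusion.** The statement is wrong as written. At the protocol's planning values, 123 patients give a 95% interval with a half-width of 10 points and a total width of 20 points, so the stated precision is overstated by a factor of two. The number 123 itself is arithmetically right for ±10 points. The most plausible explanation is a mislabelled half-width.

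The conclusion rests on the normal-approximation formula that reproduces the protocol's figure, on a prevalence of 50%, and on sensitivity and specificity of 0.80. The Wilson and Clopper-Pearson widths lead to the same conclusion. What stays open is the sponsor's intention, which matters because the text ties the 10% to clinical acceptability.

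**What to change.** Replace the precision clause with wording such as: *a 95% confidence interval with half-width 10 percentage points (total width 20 points, about 0.70 to 0.90 at 0.80)*. Keep 123 and 150. When making the change, the sponsor should confirm that ±10 points is the precision it regards as clinically acceptable. An exact lower limit could be added for information, but the correction does not need it.

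The cost is one sentence and one confirmation. The stated precision becomes less favourable; sample size, enrolment and analyses are unchanged. Should the sponsor answer that a total width of 10 points is required, the wording would stand and the sample size would not: 492 evaluable patients would be needed, or 591 with the same 20% addition (492 × 1.2 = 590.4).
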